## DURATION OF THE STUDY AND PARTICIPANT INVOLVEMENT

Study Duration: The study will open for recruitment in December 2023 and the final data will be collected before April 30^th^ 2025.

Participant Duration: We envisage an extended follow-up period of about 12 months from the time of first assessment at baseline. Considering the uncertainty about the true prevalence of tinnitus in candidates for cochlear implantation and potential disruptions to the service due to Covid-19, recruitment will continue beyond the minimum sample of 50 patients with tinnitus to recruit as many patients as possible within the duration of the study that will enable following up patients for at least 3 months.

Participants will take part in a baseline and five follow up online sessions consisting of multiple questionnaires. The baseline session will take around 45 minutes but will depend on how long the participant takes to complete each questionnaire. The frequency and duration of follow up sessions will decrease with time and will take around 15-30 minutes to complete.

### End of the Study

The end of the study will be the last assessment of the last recruited participant within the study duration.

## SELECTION AND WITHDRAWAL OF PARTICIPANTS

### Recruitment

Primary recruitment route will be from the caseload of patients in participating cochlear implantation service providers. This recruitment setting is most appropriate for this study as these services determine the eligibility to receive a unilateral cochlear implant.

Hospital interpreters and translator services will not be required for this study as participants will be required to have sufficient written or spoken English to complete online study questionnaires and give informed consent.

Potential participants will be identified and approached by members of staff considered to be members of the patient clinical care team. NHS staff will identify patients who are eligible to take part via searches of clinical databases or opportunistically during routine clinical appointments. Potential participants will be approached and informed about the study remotely via video conferencing and transcription software used for routine remote clinical appointments (e.g., Microsoft Teams), telephone, email, an invitation letter in the post as appropriate, or face-to-face if they will be attending the clinic. Remote contact will facilitate recruitment of eligible patients who may not be attending the clinic either due to awaiting surgery to receive a cochlear implant and potential burden of long-distance travel to the clinic, or other restrictions.

Approached patients will be provided with details of the CI and the study website. They will be asked to visit the study website and read the Participant Information Sheet (PIS) located on the website. They will be asked to contact the CI if they have any questions.

Participants will receive information regarding the study on the study website. Participants visiting the website will be asked to read the Participant Information Sheet (PIS) on the website before moving onto the online digital consent process. The contact details of the CI will be provided on the website and in invitation letters should the participants wish to discuss the study and their participation further or have any questions.

Posters will be displayed in the relevant clinical areas and will direct interested candidates to speak to the member of the cochlear implant team at the site, contact the CI or visit the study website for information about the study.

Secondary, non-clinical recruitment routes will include study advertisements via:

- NIHR Nottingham BRC newsletter
- Advertising on social media (e.g., NIHR Nottingham BRC Twitter, Facebook accounts)
- Online advertisements, including professional and charity organisations (e.g., BCIG, British Tinnitus Association, NCIUA)

However, potential participants will only be able to take part if their treating organisation is a research site(s) in the study.

Potential participants responding to advertisements will be asked to visit the study website, contact their clinic, or the CI via email to confirm their interest and ask any questions.

It will be explained to the potential participants that entry into the study is entirely voluntary and that their treatment and care will not be affected by their decision. It will also be explained that they can withdraw at any time, but attempts will be made to avoid this occurrence. In the event of their withdrawal it will be explained that their data collected so far cannot be erased and we will seek consent to use the data in the final analyses where appropriate.

### Eligibility criteria

The sample will comprise adults determined as eligible to receive a unilateral cochlear implant on the National Health Service (NHS) in the United Kingdom (UK).

### Inclusion criteria

- 18 years or older.
- Determined by clinical care team to be eligible for unilateral cochlear implantation and proceed to receive one.
- Sufficient written or spoken English to participate in study activities.
- Able to give informed consent.
- Did not previously receive a cochlear implant in either ear.
- Have access to internet or suitable device to complete online study questionnaires.
- Able to give informed consent.

### Exclusion criteria

- Existing or previous cochlear implant user.
- No access to computer or suitable device with internet to complete study activities.
- Unable to complete study activities independently.

### Expected duration of participant participation

Participating in the study will take 3-12 months.

### Participant Withdrawal

Participants may be withdrawn from the study either at their own request or at the discretion of the site PI under the guidance of the CI. Participants will be made aware that this will not affect their future care. Participants will be made aware (via the information sheet and consent form) that should they withdraw the data collected to date cannot be erased and may still be used in the final analysis.

Information regarding discontinuation or withdrawal of a participant will be recorded on the day of discontinuation/withdrawal in the study database. Reasons for discontinuation/withdrawal will be recorded if given. Discontinued/withdrawn participants will be replaced until the minimum target of 50 participants is reached and recruitment of new participants enables following up for at least 3 months within the duration of the study.

### Informed consent

All potential participants will be provided with a link to a secure study website Jisc by their clinician or the CI, after they have discussed the study with a member of the research team. Consent will be obtained online before completing questionnaires and extraction of relevant clinical data for the study from patient records. Consent will be completed by the potential participants alone or with the assistance of a suitably trained NHS staff as appropriate (e.g., via video conference). Signed consent will be defined as the participant entering their name, selecting a consent to each item on the consent from, and then submitting the form sent to their known contact details. PI or suitably trained NHS staff to whom consent has been delegated will be notified about digital consent and contact form being completed on the study website to verify the patient details on the contact form against the participating service records and sign the consent form. A welcome email will be then sent to the participant containing an electronic copy of the signed digital consent form, Participant Information Sheet, and the link to the study questionnaire. A copy of the signed digital consent and contact form will be stored in the electronic study forms available to view for the site PI and suitably trained NHS staff at the participating site(s). The consent will be available to print to file in the participant’s medical notes if needed.

Should there be any subsequent amendment to the protocol which might affect participation in the study, continuing consent will be obtained using an amended digital consent form which will be signed by the participant.

## STUDY REGIMEN

The study comprises two stages: a pre-operative baseline and post-operative follow up. The study will follow the steps of the cochlear implantation care pathway as shown in Figure.1. Research assessments will involve standard questionnaires completed online by study participants.

**Online questionnaires**

Participants will be asked to complete the baseline (pre-operative) questionnaire after digital consent is obtained. Participants will be asked to complete the questionnaires as soon as they can and within 2 weeks from receiving the email with the link to the questionnaire. Participants will be asked to repeat the baseline questionnaire if they are still awaiting their cochlear implantation surgery after 3 months since the first baseline questionnaire completion. Repeat baseline assessments will be optional. Participants will receive a welcome email with a copy of the signed digital consent, information on how to access the questionnaire and study website, withdraw from the study should they no longer wish to take part, and contact details of the CI should they have any questions.

Following surgery to receive their cochlear implant, participants will be asked to complete follow up questionnaires at five time points: 2 weeks after the surgery, after their first cochlear implant activation appointment, and after appointments at about 1, 3 and 6 months post implant activation (Fig. 1). These time points have been chosen to align with routine appointments in the post-operative care pathway. As such, their timing may vary according to the scheduling of those routine appointments. Participants will be sent emails with links to follow up questionnaires and asked to complete the questionnaires as soon as they can and within 2 weeks from the date their surgery and clinical appointments have taken place as indicated in the electronic study log by trained NHS staff for data extraction and entry at the site(s).

The study questionnaires will comprise a series of standard questionnaires completed according to the schedule described in Table 1. The questionnaires will be delivered online and no identifiable information will be requested (standard format including identifiers included in the application for example only). The questionnaires will include:

- **Tinnitus case profiling questionnaire (ESiT-SQ)** to comprehensively characterise tinnitus-related socio-demographic, health and lifestyle factors, sound tolerance, tinnitus presence and its characteristics and access to treatments in those who report having tinnitus (Genitsaridi et al. 2019).The full questionnaire will be completed at baseline, while a modified subset of questions will be used at follow up to establish the presence of tinnitus and changes in related characteristics since previous assessment.
- **Tinnitus Functional Index (TFI)** to assess the impact of tinnitus on the patients reporting tinnitus (Meikle et al. 2012). NICE has recommended the TFI for the assessment of tinnitus impact in adults (NICE 2020), and changes on TFI will be used to address the primary objective of the study. Participants who do not experience tinnitus will not complete this questionnaire.

.

- **Patient Health Questionnaire (PHQ-9)** to assess the presence and severity of depressive symptoms (Kroenke et al. 2001). The PHQ-9 is a standard diagnostic questionnaire widely used in both clinical settings and research studies, including assessments of depressive symptoms in patients with tinnitus (Wallhausser-Franke et al. 2017; Aazh & Moore 2019).
- **Generalized Anxiety Disorder (GAD-7)** to assess the presence and severity of anxiety symptoms (Spitzer et al. 2006). The GAD-7 is a standard diagnostic questionnaire widely used in both clinical settings and research including studies assessing anxiety in the general tinnitus population (Aazh & Moore 2019), and cochlear implant recipients (Olze et al. 2011; Bruggemann et al. 2017).
- **Insomnia Severity Index (ISI)** to assess the presence, severity and nature of insomnia symptoms (Bastien et al. 2001). The ISI has been found to be a reliable measure for detecting clinically abnormal insomnia symptoms (Smith & Wegener 2001; 2003; Gagnon et al. 2013). It has been widely used in studies investigating insomnia in the general tinnitus population (Miguel et al. 2014; Cronlein et al. 2016; Aazh & Moore 2019), cochlear implant recipients (Pierzycki & Kitterick 2021), and clinical trials evaluating effectiveness of interventions for insomnia (Curtis et al. 2021).
- **Two Quality of Life (QoL) questionnaires** to assess changes in (a) hearing-related quality of life using the Health Utilities Index Mark 3 (Feeny et al. 1995) and (b) health-related quality of life using the EuroQol EQ-5D-5L questionnaire (Herdman et al. 2011). Both questionnaires will be used as Health Utilities Index Mark 3 is used by NICE in recommendations for the provision of cochlear implantation in the UK (NICE 2019a), while EQ-5D is the preferred instrument by NICE to measure health-related quality of life with the ‘5L’ version supported for use in prospective clinical studies (NICE 2013, 2019b). The EQ-5D has been also shown to be sensitive to changes in tinnitus and recommended for evaluating interventions intended to alleviate tinnitus (Summerfield et al. 2019).
- **Speech, Spatial and Qualities 12 (SSQ-12)** to assess hearing function in everyday situations (Noble et al. 2013). The SSQ has been found to be sensitive for detecting listening difficulties associated with changes in the severity of hearing loss in the general population (Gatehouse & Noble 2004; Singh & Pichora-Fuller 2010), and an efficient and sensitive measure of changes in self-reported hearing function in cochlear implant recipients (Wyss et al. 2019).

| Figure 1. Study flow chart. |
| --- |
| [figure not shown] |

Table 1. Schedule of online questionnaires.

| **Assessment**  * if tinnitus present  CI = cochlear implant | **Baseline** | **Follow up** | | | | |
| --- | --- | --- | --- | --- | --- | --- |
|  | **pre CI surgery** | **2 weeks post CI surgery** | **CI activation** | **1 month post CI activation** | **3 months post CI activation** | **6 months post CI activation** |
| **Recruitment** |  |  |  |  |  |  |
| Digital consent & contact form | X |  |  |  |  |  |
|  |  |  |  |  |  |  |
| **Tinnitus case profiling questionnaire** |  |  |  |  |  |  |
| ESiT-SQ (Part A & B*) | X |  |  |  |  |  |
| **Tinnitus impact (primary outcome)** |  |  |  |  |  |  |
| Tinnitus Functional Index* | X | X | X | X | X | X |
|  |  |  |  |  |  |  |
| **Psychological symptoms** |  |  |  |  |  |  |
| Patient Health Questionnaire 9 | X | X |  | X | X | X |
| Generalized Anxiety Disorder 7 | X | X |  | X | X | X |
| Insomnia Severity Index | X | X |  | X | X | X |
|  |  |  |  |  |  |  |
| **Quality of life** |  |  |  |  |  |  |
| EuroQoL EQ-5D-5L | X |  |  |  | X | X |
| Health Utilities Index Mark 3 | X |  |  |  | X | X |
|  |  |  |  |  |  |  |
| **Hearing function** |  |  |  |  |  |  |
| Speech, Spatial, Qualities 12 | X |  |  |  | X | X |
|  |  |  |  |  |  |  |
| **Tinnitus presence & characteristics* follow up** |  |  |  |  |  |  |
| ESiT-SQ (subset) |  | X | X | X | X | X |

### Compliance

Due to observational nature of study, compliance will not be monitored. To minimise non-compliance participants will be encouraged to complete questionnaires as soon as possible and within 2 weeks of sending the questionnaire link before it expires. Two automated reminders will be sent within the 2-week period (after day 5 and 10) if questionnaires are not completed by that time.

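### The baseline link expires after two weeks and the repeat baseline depends on completing the first, so a late responder has no stated route to a pre-operative baseline

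*Protocol*

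**What the plan says.** Under Online questionnaires (Study Regimen), the baseline is tied to consent and not to the surgery date: "Participants will be asked to complete the baseline (pre-operative) questionnaire after digital consent is obtained". It is due "within 2 weeks from receiving the email with the link to the questionnaire".

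Under Compliance, the same limit is set for questionnaires in general, to be completed "within 2 weeks of sending the questionnaire link before it expires". The two automated reminders fall after days 5 and 10, both inside the window. The section also states: "Due to observational nature of study, compliance will not be monitored".

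For long waits, Online questionnaires asks participants to repeat the baseline "if they are still awaiting their cochlear implantation surgery after 3 months since the first baseline questionnaire completion". It adds: "Repeat baseline assessments will be optional".

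Follow-up links are sent according to the surgery and appointment dates that sites enter in the electronic log. As written, they do not depend on a completed baseline.

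**The concern.** At follow-up a short window has a purpose: it keeps the answer close to the event it describes. Baseline has no such event. Table 1 requires only that it precede implant surgery, and the protocol itself expects some patients to wait beyond three months. Closing the link after two weeks can shut out someone who is still fully able to give a valid baseline.

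The repeat does not help, because its clock starts at a completion that never took place. The people offered a second invitation are those who already answered the first.

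Baseline is the one assessment that cannot be collected later. A patient who misses one follow-up still has four others. A patient who misses baseline has no pre-operative TFI, no pre-operative tinnitus status and no full ESiT-SQ, which is scheduled at baseline only. Missed baselines are also plausible: this is the longest session (about 40 minutes in the Synopsis, around 45 under Duration of the Study, against 15–30 for follow-ups), and vouchers are paid only at the final assessment.

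**Working it through.** **1. Following the rules for one late responder**

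- Consent is given and the baseline link is sent: day 0.
- Reminders: after days 5 and 10. Link expires: day 14.
- No section describes re-issuing an expired baseline link or leaving it open.
- Three-month repeat: counted from first completion. With no completion, the condition is never met.
- Replacement (Participant Withdrawal): covers discontinued or withdrawn participants. A missed baseline is not mentioned.
- Surgery is logged and follow-up links go out. Post-operative TFI and tinnitus presence can be collected, but there is no pre-operative value to set them against.

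**2. What is lost and what is kept**

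- Lost: change in TFI (primary objective), pre-operative prevalence, new incidence after implantation.
- Kept: post-operative nature and severity of tinnitus, and post-operative comparisons of patients with and without tinnitus, because the ESiT-SQ subset is scheduled at all five follow-ups, as is the TFI for those with tinnitus.

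**3. The protocol's own sample size**

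Inputs from Sample size and justification: SD 25.1, difference 17.9, correlation 0.3, one-tailed 0.05, attrition 38%.

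- SD of change = 25.1 × √(2 × (1 − 0.3)) = 29.70
- Standardised change = 17.9 / 29.70 = 0.603
- With 31 pairs, one-sided power (noncentral t) = 94.9%. The protocol states no power.
- 31 / (1 − 0.38) = 50

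The figures of 31 and 50 are consistent with each other.

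**4. Illustrative size**

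The documents give no rate of missed baselines. Assume 10–20%, unrelated to tinnitus status. Prevalence of 50–80% is the protocol's range.

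- Patients with tinnitus but no baseline, per 100 consented: 100 × 0.10 × 0.50 = 5 up to 100 × 0.20 × 0.80 = 16.
- Consents needed for 50 patients with tinnitus and a baseline = 50 / (prevalence × (1 − miss rate)), rounded up:

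| Prevalence | No misses | 10% missed | 20% missed |
| --- | --- | --- | --- |
| 50% | 100 | 112 | 125 |
| 80% | 63 | 70 | 79 |

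**5. A pessimistic bound**

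Suppose the missed baselines fell inside the 50 and came on top of the 38%. Pairs = 50 × 0.62 × (1 − miss rate), rounded down. A 10% miss rate gives 27 pairs and 92.0% one-sided power; 20% gives 24 pairs and 88.9%. Even then the loss of power is modest. The documents do not establish either supposition.

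**The case against.** The strongest reply is that expiry of a link is an operational setting and not a bar to late data. Participants are only asked and encouraged to answer within two weeks, and nothing says that a late baseline is rejected. Staff have the means to re-send: Case Report Forms describes site logs for sending questionnaire invitations and contact details held in case further follow-up is needed, and participants have the Chief Investigator's details. This stands. A reader might infer that the baseline is irretrievably lost, but the text supports only that no route is provided. With compliance unmonitored, nothing prompts anyone to use the means that exist.

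A reader might also infer that the study will fall short of its 31 pairs, or that the loss adds to the 38% attrition. Neither is supported. Patients whose pre-operative tinnitus status is unknown would not be counted among the 50, and recruitment continues to at least that number and beyond. The 38% was chosen because of the new online, patient-led collection method, so it may already allow for missed baselines in number. It does not address who is missed.

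A further objection is that an open window mixes early waiting-list states with immediate pre-operative ones, which could matter for PHQ-9, GAD-7 and ISI. This has little force. The baseline-to-surgery interval already varies under the current plan, and for late responders it would only be shorter than if they had answered on time.

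**Conclusion.** The point holds as a badly fixed rule. Followed as written, the two-week expiry and the completion-based repeat together leave a consented, still pre-operative late responder without a stated way to give a baseline, and so outside TFI change, pre-operative prevalence and new incidence.

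The cost falls on yield and representativeness: fewer usable participants per consent, and possibly a selected set, since slow responders may differ from prompt ones. The documents give no figure on that selection. The numerical size rests wholly on the assumed 10–20% miss rate and on no baseline being recovered by an informal re-send.

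It would go too far to say that all objectives fail for these patients, because their post-operative data still serve parts of secondary objectives 2 and 3. The powered comparison is not shown to be at risk.

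**What to change.** Amend Online questionnaires and Compliance as follows.

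- Exempt baseline from the two-week expiry: keep the link open, or re-issue it with automated reminders, until surgery.
- Accept as baseline any questionnaire dated before the surgery date in the site log.
- Time the three-month invitation from consent or first invitation, so that those who did not complete the first baseline are included. Because the repeat is optional, someone who has just answered can decline it.
- Record the interval from baseline to surgery for every participant.
- Keep the two-week expiry for follow-ups.

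The cost is a setting in the online system, a few more automated reminders and a short protocol edit. Sites already log surgery dates, and reminders are already automated. The downside is a wider spread in baseline timing relative to consent and surgery, which the recorded interval allows the analysis to describe or adjust for.

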### Criteria for terminating the study

No stopping points will be defined other than the study end date.

# ANALYSES

### Methods

Data analyses will be conducted by the study team with support from medical statisticians at the NIHR Nottingham BRC and/or the University of Nottingham. The software utilised for analyses may include Excel, SPSS, R or MATLAB. The data generated from statistical analysis will be stored and backed-up on the University of Nottingham servers.

Detailed analyses will be specified prospectively in the study analysis plan developed by the study team. Mixed statistical methods will be used to characterise the sample and evaluate changes in the severity of tinnitus and patient-specific factors before and after implantation. Data analyses will include descriptive statistics, General/Generalized Linear Models (e.g. ANOVA, regression models) or non-parametric statistical methods where appropriate (e.g. Mann Whitney U test). Participants may be grouped according to their socio-demographic and relevant patient-specific characteristics, including the presence, severity and nature of tinnitus, hearing-related outcomes, psychological symptoms and factors related to cochlear implantation or device use. We will seek to construct regression models to explore associations between the severity of tinnitus and existence/severity of psychological symptoms, socio-demographic variables, hearing-related outcomes and quality of life in patients with and without tinnitus (Pierzycki et al. 2016; Pierzycki & Kitterick 2021).

